#### Behavioral assessments

The CRS-R consists of 23 items arranged hierarchically and divided into six subscales (auditory, visual, motor, oromotor/verbal, communication, and arousal) that test for arousal and awareness in DoC patients (49). The score is based on the presence or absence of behavior in response to stimuli. The total quantitative score is calculated in addition to the best response observed in each subscale. The diagnosis is based on the nature of the best responses observed overall. To overcome the limitation of overlapping total scores for two different diagnoses, the CRS-R index score will be used as well for statistical purposes (50). The validated version for German and French speaking patients will be used accordingly in the study sites (51, 52). The Disability Rating Scale (DRS) is a tool for the quantitative assessment of the severity of brain injuries. It consists of four categories: arousal and awareness, cognitive abilities, physical and psychosocial independence (41). The Glasgow Outcome Scale – Extended (GOS-E) is an interview tool rating the severity of the cognitive, physical, and psychosocial consequences after severe brain injury in the form of an interview with the primary caregiver. It rates the functionality of the patient from death to complete remission (42).

#### EEG

High-density resting state EEG will be recorded using a BrainVision device (BrainAmp, BrainProducts, GmbH, Gilching, Germany). EEG signals will be measured in microvolts, sampled at 500 Hz and referenced to the vertex (Cz) using 64-channels TMS-compatible EEG nets. During the 15 min of recordings in Study 1 and 2, patients will be kept awake (e.g., eyes open) by the experimenter. EEG signals are sensitive to movements and DoC patients are often unable to comply with the instruction to stay still during the recordings. Therefore, in case of agitation or heavy artifacts, recording times will be adapted to obtain enough data to perform the analyses. The resting state data will be used to obtain spectral power and brain connectivity using the graph theory, which have proven to correlate with behavioral recovery of patients with DoC (35).

#### TMS-EEG

The simultaneous use of TMS with EEG implies the perturbation of the brain with a magnetic pulse while recording brain activity electrophysiologically in response to the stimulation. TMS-EEG has become a promising tool in assessing different brain states and functionality (e.g., neural plasticity) over the past two decades (46, 53). The PCI is a mathematical index that expresses the complexity of the brain response to the magnetic perturbation and can successfully discriminate between different brain states (31, 54, 55). In the present protocol, the PCI will be used as a secondary outcome to determine the neurophysiological effects of the 4 weeks rTMS intervention. For TMS-EEG measurements, the coil will be positioned over the premotor area and the precuneus using neuronavigation based on the individual’s T1-weighted MRI or CT images. The stimulation will be individualized depending on the brain responses (first peak-to-peak around 10 μV, and 0.4–0.5 Hz frequency). The jittering of the perturbation (2–2.3 s) should avoid patients building up habituation effects regarding the repetitive stimulation. Once a spot has been found to give appropriate responses as displayed by the general user interface of the machine, a total of 300 pulses will be applied per area (i.e., premotor area and precuneus), which results in a protocol duration of approximately 10 min per area. Noise-masking will be applied via in-ear headphones to avoid auditory late cognitive potentials due to the magnetic stimulation. Moreover, if somatosensory artifacts were to be detected, a thin foil would be placed between the coil and the scalp to reduce skin movement induced by the field.

### Power calculation

There are currently no RCTs available in the literature simultaneously testing the effects of DLPFC and AG rTMS in patients with DoC. As no clear-cut information could be drawn from the literature, a dedicated power analysis was done using G*Power software (56). Assuming a medium effect size of *f* = 0.5 at an alpha error level of 0.05 and a power of 0.8 with ANOVA or multiple regression analysis, 74 patients need to be recruited to detect meaningful differences in the primary outcome (CRS-R) between the real versus sham stimulation groups. Considering a 20% dropout ratio, the number of patients to be recruited adds up to 90.

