#### Personalized parallel trial

This trial will include three arms (i.e., DLPFC rTMS, AG rTMS and the sham-controlled condition). After a 1 week washout period following the randomized crossover study, the personalized parallel trial will be conducted. Based on their behavioral (primary) or electrophysiological (secondary) responses to either the left DLPFC or left AG treatment in the crossover RCT, patients will be assigned to one of two groups (i.e., DLPFC group if the patient was a responder to the DLPFC stimulation; AG group if the patient was a responder to the AG stimulation). If no behavioral response nor EEG change from the RCT could be obtained regarding the best stimulation hotspot or if the patient is a responder to both sites, the patient will be randomized into one of the two stimulation hotspots in a 1:1 ratio. Then, all patients will be randomized between the experimental condition and the sham condition following a 2:1 ratio by a randomized order generator. Only the investigator in charge of the randomization will be aware of the patients’ group allocation. The assigned intervention (i.e., active stimulation versus sham stimulation) will be concealed from the patient, the family, the care providers and all investigators involved in the patient’s assessment for the whole duration of the treatment phase. The evaluator will stay blind from the sequence as well as from the stimulation group during treatment and follow-up. Moreover, analyses will be conducted in a triple blind fashion (see *rTMS device* point for more information about blinding methods). All patients included in the trial will undergo 4 weeks (i.e., 20 working days) of stimulation. Behavioral effects will be assessed with the CRS-R at baseline and once a week during the 4 weeks stimulation protocol. Fifteen minutes of high-density EEG resting state will be performed right before and right after the first session as well as before and after the last session. Eventually, TMS-EEG acquisitions will be performed the first and last day of the 4 weeks protocol. As we will assess the effects following a single session (first stimulation session) and after 4 weeks of rTMS, we will be able to compare the effect of a single versus repeated sessions of stimulation. Figure 3 depicts an overview of the two studies.

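### The power statement does not hold: f = 0.5 is not a medium effect, 74 does not follow from it, a medium effect has about 52% power at 2:1, and 90 less 20% is 72

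*Protocol article*

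**What the plan says.** The Power calculation section rests on a G*Power analysis in which Cohen's f is set to 0.5 and called medium. Its result reads: "at an alpha error level of 0.05 and a power of 0.8 with ANOVA or multiple regression analysis, 74 patients need to be recruited". The comparison in view is CRS-R under real against sham stimulation. For dropout the section adds: "Considering a 20% dropout ratio, the number of patients to be recruited adds up to 90". The number of groups, the number of predictors and the sidedness are not given.

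The Personalized parallel trial section describes three arms (DLPFC, AG and sham) and randomises active to sham "following a 2:1 ratio by a randomized order generator". The Data analysis section measures group effects by pre-to-post differences and expresses the effect size as Cohen's d on the change from baseline, active against sham.

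**The concern.** The label and the number conflict: 0.5 is the conventional medium value for d, not for f. A mix-up of the two scales is plausible, since the Data analysis section works in d, but the document does not settle the cause. If the label is meant, 74 is far too few. If the number is meant, 74 is far more than needed. The dropout inflation also falls short of its own target.

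This paragraph is the article's only justification for enrolling 90 patients. A reader who trusts it will believe that the real-versus-sham comparison has 80% power for a medium effect, and will read a null result in the parallel trial accordingly.

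**Working it through.** **Inputs.** Effect size f = 0.5 labelled medium, alpha 0.05, power 0.80, N = 74, dropout 20% and recruited N = 90 come from Power calculation. The 2:1 ratio and three arms come from Personalized parallel trial. Assumptions: a two-sided test (an F test is non-directional), no covariate adjustment, and the active arms pooled against sham.

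**Step 1: the scale.** For two equal groups f = d/2, so f = 0.5 means d = 1.0. The usual values for f are 0.25 (medium) and 0.40 (large).

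**Step 2: try to reproduce 74.** Noncentral F with noncentrality λ = f²·N, alpha 0.05, power 0.80:

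| Groups in one-way ANOVA | N at f = 0.5 | N at f = 0.25 (equal groups) |
|---|---|---|
| 2 | 34 | 128 |
| 3 | 42 | 159 |
| 4 | 48 | 180 |

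Other readings were also tried:

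- Multiple regression with f² = 0.5² = 0.25, testing all predictors: 34 for one predictor, 72 for nine, 75 for ten. The sequence skips 74.
- Repeated-measures ANOVA at f = 0.5 (2 or 3 groups, 2 to 6 measures, correlation 0 to 0.8): 4 to 38.
- 0.5 read as d, two-sided two-sample t-test: 128 at 1:1, 144 at 2:1. One-sided: 102 and 114. Paired, two-sided: 34.

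None gives 74. At N = 74, f = 0.5 would give 98.9% power with two equal groups and 97.3% with three, not 80%.

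**Step 3: power of the 2:1 parallel trial.** Two-sided t-test at 5%, noncentrality d·√(n₁n₂/(n₁+n₂)). For 49 v 25 and d = 0.5 this is 0.5·√(1225/74) = 0.5·4.07 = 2.03, on 72 degrees of freedom.

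| Completers (active v sham) | Power, d = 0.5 | Power, d = 1.0 | d detectable with 80% power |
|---|---|---|---|
| 74 (49 v 25) | 51.9% | 98.0% | 0.70 |
| 72 (48 v 24) | 50.5% | 97.6% | 0.71 |

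With no dropout (60 v 30), power for d = 0.5 is 59.9%. Reaching 80% for d = 0.5 at 2:1 takes 144 completers (96 v 48). At 2:1, f = d·√(2/3·1/3) = 0.471·d, so d = 0.71 corresponds to f of about 0.33.

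**Step 4: dropout.**

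- Correct inflation: 74/(1 − 0.20) = 92.5, so 93.
- 74 × 1.2 = 88.8; rounding this up would explain 90.
- 90 × 0.8 = 72, which is below 74.
- 90 recruited covers 1 − 74/90 = 17.8% dropout.

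**The case against.** - **The 52% is conditional.** It takes the word medium over the number 0.5. If d = 1.0 was meant, the parallel trial has about 98% power and is not under-powered. This stands as a caveat, but 98% is not the stated 80% either, and 74 is still unexplained.
- **The assumed test may be too pessimistic.** One-sided, 49 v 25 gives 64%. If d = 0.5 were on the post-score SD and the analysis adjusted for baseline, 48 v 24 would give 54%, 62%, 69% and 79% at assumed baseline correlations of 0.3, 0.5, 0.6 and 0.7. The article gives no correlation, and it standardises on change from baseline, which weakens the point.
- **The crossover is stronger.** A paired comparison with d = 0.5 and 72 patients has about 99% power. That is right, and the shortfall does not apply there. But the section speaks of real versus sham groups, which describes the parallel trial.
- **Exact scale at 2:1.** There f = 0.25 corresponds to d = 0.53, with 55% power (72) or 57% (74). This is a small difference.
- **A model giving exactly 74 exists.** Testing 9 of 20 predictors at f² = 0.25 does so. No such model is described, and it would not test real against sham.
- **An article may leave detail to the full protocol.** The missing number of groups or predictors is not counted as an error here. The finding rests on figures that are stated and conflict.
- **The dropout slip is small.** It is 93 against 90, or about 1.4 points of power, and is secondary.

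**Conclusion.** The concern holds. f = 0.5 is mislabelled as medium. The figure of 74 follows from neither f = 0.5 nor f = 0.25 under any two-, three- or four-group ANOVA. The recruited 90 does not cover the stated 20% dropout.

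For a true medium effect (d = 0.5), the 2:1 parallel trial has about 52% power with 74 completers and about 50% with the 72 that remain after dropout. With 80% power it detects d of about 0.70 to 0.71. These figures assume a two-sided 5% test, pooled active against sham, unadjusted, with d on the change score. Sidedness or baseline adjustment would change the size of the shortfall. They would not repair the label, the derivation of 74 or the gap between 72 and 74. No power problem is claimed for the crossover phase.

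**What to change.** Keep N = 90 and rewrite the Power calculation section:

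- Delete the description of f = 0.5 as a medium effect, and the 74 derived from it.
- Replace it with, for example: *With 90 patients enrolled and 20% dropout, 72 completers (48 active, 24 sham) give the parallel trial 80% power at two-sided alpha 0.05 to detect d = 0.71 (f about 0.33), and about 50% power for a medium effect of d = 0.5.*
- If 74 is kept as a target for any reason, say that 90 enrolled covers 17.8% dropout, not 20%.
- Name the test, the number of groups and the allocation behind the figure, and say that it concerns the parallel trial. Give the crossover its own statement if one is wanted.
- Say that the figure is for a single comparison at 5%. The Data analysis section applies a Holm correction and makes both the CRS-R total and index scores primary, so power would be lower wherever that correction reaches the primary comparison.

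The cost is wording in the protocol and analysis plan, with no extra patients and no design change. The stated power becomes less favourable.

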### Electronic data collection and management

All data collected during this study will be processed and anonymized by an identification number which code will only be known by the researchers involved in the study and will therefore be handled confidentially. Electronic data will be protected by firewall. The researcher in charge will keep the personal data in a file dedicated to the study. All data will be stored and shared between institutions onto Research Space RSpace^©^ – an online secured server providing database security and protection against malicious use. These case report forms (CRF) will be filled out in print and safely stored in lockers inside the clinic and only accessible to the research staff. Patient data will be pseudonymized in all CRF files. These data will be the subject of presentation and scientific publications, in which the identity of the participating patients will be anonymized.

### Data analysis

#### Primary outcomes

For both crossover and longitudinal trials, primary analyses will focus on the detection of behavioral changes (i.e., enhanced behavioral total scores and/or changes in the level of consciousness as defined by the CRS-R) at the group level, comparing the sham interventions to the active interventions; and at the individual level, comparing post treatment to pre-treatment data. Along the same lines, analyses will also offer a comparison of the effects of frontal and parietal active rTMS on patients’ behavioral scores following one session of stimulation for the crossover RCT, and 4 weeks of stimulation for the longitudinal trial. Behavioral CRS-R total scores and subsequent index scores (50) will be defined as our primary outcome. Group treatment effects will be assessed with calculation of the difference between each group post-treatment and pre-treatment score means. Furthermore, we will identify clinical responders to (1) a single session of rTMS in the crossover trial and (2) the 4 weeks treatment protocol of the longitudinal trial as patients who will display new sign(s) of consciousness following treatment that was not present at baseline nor during the screening phase. In that context, further subgroup analyses will also be conducted along age, etiology, time since injury and diagnosis at inclusion.

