#### Randomized crossover trial

Within 10 days, all patients will undergo four rTMS sessions that will be administered in a randomized order and separated by a 72 h washout period: (i) one real stimulation over the left DLPFC, (ii) one real stimulation over the left AG, (iii) one sham stimulation over the left DLPFC, and (iv) one sham stimulation over the left AG. In this study, we chose to stimulate the left hemisphere because it tends to be more often targeted in non-invasive brain stimulation trials with DoC patients than the right hemisphere and because it was shown to have more promising results in other top-down electromagnetic-based techniques such as transcranial direct current stimulation (40). Randomization of the sequence of the four stimulation sessions will be stratified for gender, etiology, time post-injury, and diagnosis using computerized random number generator. Standardized behavioral assessments will be performed by experienced clinicians who will be blind to the nature of the sessions. The CRS-R will be performed before and after each stimulation session. Fifteen minutes of resting state high-density EEG will be performed directly before and after the stimulation (i.e., after the behavioral evaluation pre-stimulation and before the behavioral evaluation post-stimulation). Together with the EEG, electrooculogram (EOG) and electrocardiogram (ECG) will be recorded. See Figure 2 for the randomized crossover trial protocol.

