**Figure 3 fig3:**
[figure not shown]
Overall protocol overview. After Study 1, patients who showed behavioral or EEG improvements following stimulation (either frontal or parietal) will be attributed to the corresponding group in Study 2. Patients who showed no improvement following either stimulation types will be randomized between the frontal and the parietal stimulation group in a 1:1 ratio. All patients will then be randomized between active and sham conditions in a 2:1 ratio. In Study 2, patients will be randomly assigned to either the active or the sham condition and will receive a longitudinal treatment protocol. The treatment phase will consist of stimulation sessions applied 20 min per day, 5 days a week during 4 weeks for a total of 20 stimulations sessions. Baseline (first day of stimulation, before the session) and post-treatment (last day of stimulation, after the session) assessments will include the CRS-R, 15 min resting state EEG and TMS-EEG to compute PCI. Follow-up measures (CRS-R and resting state EEG) will be collected at +1 and + 2 weeks following the end of the treatment phase. At 3 and 6 months following the end of the treatment phase, functional outcomes will be collected.

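### In the parallel phase, the primary CRS-R effect is a plain pre-post difference in means. Baseline adjustment and the weekly scores would make it more precise at no extra data cost.

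*Protocol article*

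**What the plan says.** The Primary outcomes section covers both trials. It names the endpoint, "Behavioral CRS-R total scores and subsequent index scores (50) will be defined as our primary outcome", and sets the contrasts as "comparing the sham interventions to the active interventions; and at the individual level, comparing post treatment to pre-treatment data". It then gives the group-level estimator: "Group treatment effects will be assessed with calculation of the difference between each group post-treatment and pre-treatment score means". No covariate is named. The closing paragraph of Data analysis builds Cohen's d on the same baseline-to-post difference between active and sham.

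The data collected in the parallel phase are richer than that estimator needs. Personalized parallel trial states: "Behavioral effects will be assessed with the CRS-R at baseline and once a week during the 4 weeks stimulation protocol". The Figure 3 caption places baseline before the first session and the post-treatment assessment after the last one, and adds: "Follow-up measures (CRS-R and resting state EEG) will be collected at +1 and + 2 weeks following the end of the treatment phase". No analysis paragraph in the article says how the intermediate weekly scores will be used.

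The crossover has a different structure: "The CRS-R will be performed before and after each stimulation session". It has one score before and one after each session, and no weekly series.

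The crossover sequence is stratified by gender, etiology, time post-injury and diagnosis. The 2:1 active-sham randomisation of the parallel phase is described without any stratification factor.

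**The concern.** The sample runs from UWS/VS to MCS, so baseline CRS-R should be strongly related to CRS-R four weeks later. A change score subtracts the whole baseline, which amounts to a regression slope of 1. When the correlation is below 1 and the variances are equal, the best slope is rho, so the change score over-corrects. The result is extra variance and an estimate that moves with any chance baseline difference between the arms. With a 2:1 split and no named stratification, such a difference is not unlikely.

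A two-point estimator also makes no use of weeks 1-3. For a patient who leaves after week 1, those scores carry information about week 4. Both losses can be avoided with variables the trial already records.

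**Working it through.** **The plan's own figure.** Power calculation gives 74 evaluable patients and 90 recruited, from "Assuming a medium effect size of *f* = 0.5", alpha 0.05 and power 0.8. A two-group ANOVA with f = 0.5 needs 34, so 74 does not follow from the stated inputs. For dropout, 74 x 1.2 = 88.8 (89) is close to 90, whereas 74/0.8 = 92.5 gives 93. This is a separate matter. It means only that the 80% starting power used below is a reference point and not an established property of the trial.

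**Inputs.** 74 patients at 2:1 are about 49 active and 25 sham. The correlation rho between baseline and week-4 CRS-R is not in the document, so a range is shown. Variances before and after treatment are taken as equal and set to 1.

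**Step 1: precision.**
- Change score, variance per patient: 2(1 - rho).
- Baseline-adjusted (ANCOVA): 1 - rho².
- Ratio: (1 - rho²) / [2(1 - rho)] = (1 + rho)/2.

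| rho (assumed) | Adjusted / change variance | Reduction | Patients giving the precision of 74 under the change score | Power at 49:25 if the change score had 80% |
|---|---|---|---|---|
| 0.5 | 0.75 | 25% | 55.5 | 90% |
| 0.6 | 0.80 | 20% | 59.2 | 88% |
| 0.7 | 0.85 | 15% | 62.9 | 86% |
| 0.8 | 0.90 | 10% | 66.6 | 84% |
| 0.9 | 0.95 | 5% | 70.3 | 82% |

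The fourth column is 74 x (1 + rho)/2. The last column divides the effect detectable with 80% power at 49:25 (d about 0.70) by the square root of the ratio and recomputes power with the noncentral distribution.

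**Step 2: baseline imbalance.** Given an observed baseline difference D between arms, the change score is off by (1 - rho)D in size. One standard error of D at 49:25 is sqrt(1/49 + 1/25) = 0.25 SD. The shift is then 0.5 x 0.25 = 0.12 SD at rho 0.5 and 0.2 x 0.25 = 0.05 SD at rho 0.8. This is not a second loss on top of step 1. Since 2(1 - rho) = (1 - rho²) + (1 - rho)², the excess variance of the change score is exactly this imbalance term averaged over randomisations.

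**Step 3: weekly scores.** With complete data, a mixed model that has a separate treatment effect at each week gains essentially nothing at week 4 over ANCOVA. Its gain comes from patients who leave early. The article's only dropout figure is in "Considering a 20% dropout ratio". Assume 20% monotone dropout, completely at random, spread evenly over the four weeks (5% each). Comparing the week-4 information with that of complete-case ANCOVA gives a further variance reduction of about 3-7%, depending on the correlation pattern. Under compound symmetry it is about 3% at rho 0.6 and 5% at rho 0.9. Combined with step 1:
- rho 0.6: 0.80 x 0.97 = 0.78, a total reduction of about 22-23%;
- rho 0.9: 0.95 x 0.95 = 0.90, a total reduction of about 9-10%.

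**Crossover.** Each patient receives all four conditions. The 2:1 split, the weekly series and the formulas above do not carry over, and no figure is given for that phase.

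**The case against.** The strongest reply is that this is a condensed article whose SAP is not shown, and that covariates, longitudinal models and missing-data rules usually sit there. Power calculation also refers to ANOVA or multiple regression, which can carry a baseline covariate. That stands in part: nothing in the article forbids adjustment. But the reference to regression concerns sample size and names no covariate. The estimator in Primary outcomes is stated, and Cohen's d repeats it. The point concerns what is written, not what is left out.

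It is also fair that a change score does use baseline, by subtraction, and is unbiased under randomisation. What it lacks is regression adjustment, so the issue is efficiency rather than validity. At rho 0.9 the gain is small.

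Three stronger readings are tempting, and the document does not support them.
- A reader might infer a completer-only analysis. A pre-post difference needs some rule for patients with no final score, but the article states neither an exclusion nor an imputation rule. Dropout appears only as a sample-size inflation, so a completer bias cannot be charged to the plan.
- A reader might infer that the trial is short of power. At 49:25, power is 98% for d = 1.0 (the stated f = 0.5 for two equal groups) and 52% for d = 0.5. The answer depends on which effect is meant. At the stated effect there is little power left to gain.
- A reader might infer that weekly data would restore the 20% expected to drop out. They do not. The gain is the 3-7% in step 3, and a patient lost before week 1 has no post-baseline score to contribute.

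**Conclusion.** The concern holds for the parallel phase as a loss of precision. The stated estimator is valid but inferior to baseline adjustment whenever rho is below 1. The avoidable variance is 25% at rho 0.5, 10% at 0.8 and 5% at 0.9. The weekly scores add roughly 3-7% under 20% dropout completely at random. These sizes rest on an assumed correlation, equal variances and an assumed dropout pattern, none of which the article gives. The direction does not depend on the particular rho, but the size does. The change is worth making because it needs no new data. It should be settled before unblinding, since choosing the adjustment afterwards would be open to the charge of being data-driven.

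**What to change.** For the parallel phase, replace the sentence on group treatment effects with a baseline-adjusted analysis of all randomised patients. This would be a repeated-measures mixed model of weekly CRS-R (weeks 1-4) with baseline CRS-R, diagnosis, target group (DLPFC or AG), week, treatment and treatment-by-week. The active-sham contrast at week 4 would be primary, with week 4 identified as the last-day assessment in the Figure 3 caption. Target group is settled before the 2:1 randomisation, so it is a legitimate baseline covariate. The same model can be fitted to the total score and the index score. Report the adjusted difference with its confidence interval beside Cohen's d.

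For the crossover, a mixed model of the post-session score with pre-session score, period and condition as fixed effects and patient as a random effect is a reasonable parallel change, offered without a claimed gain.

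The cost is analysis wording only. Every variable is already collected, and visits, sample size and randomisation are unchanged.

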## Study objectives and hypotheses

Although the choice of stimulation site is becoming an increasingly important issue in the neurostimulation community, no clinical RCT has been performed to determine which stimulation site might be associated with the best clinical outcomes after severe brain injury. Hence, this is the study’s main objective. In a second phase, we will provide a patient-tailored individualized therapy approach through a personalized medicine design. We aim to (1) improve the functional recovery of patients with DoC using either frontal or parietal rTMS, (2) investigate the neurophysiological effects of rTMS interventions in these two distinct brain areas using resting state electroencephalography (EEG) and TMS-EEG, (3) determine the phenotype of clinical responders (i.e., that is, any patient who displayed new sign(s) of consciousness following stimulation that was never displayed during the screening phase nor at baseline), and (4) assess the long-term efficacy of the rTMS interventions in terms of functional outcomes through follow-up assessments.

Our primary hypothesis for the RCT crossover is that a significant portion of our patient sample will show increased responsiveness (i.e., overall CRS-R scores and signs of consciousness) following a single session of DLPFC or AG rTMS (responders). We also expect some patients to show stronger EEG connectivity at the whole brain level, especially in frontoparietal regions (20) compared to sham stimulation.

As for the second phase of the study, as a primary outcome, we hypothesize that patients stimulated over the left DLPFC or the left AG for 20 consecutive sessions will show higher levels of behavioral improvement compared to patients in the sham stimulation group.

Moreover, as secondary hypotheses, we expect that these changes in responsiveness will be associated with modifications in brain complexity and functional connectivity. We postulate that the EEG resting state metrics (e.g., spectral power metrics, connectivity) in the frequencies of interest (i.e., delta, theta and alpha bands) and the TMS-EEG derived measures of brain responses (e.g., PCI) will be modulated by the rTMS intervention and associated with behavioral responses to therapy.

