### Procedure

#### Screening phase & enrollment

The study procedure will start at the earliest on the 28th day post-injury. All patients will be evaluated repeatedly (i.e., at least twice within 10 days prior to inclusion) with the CRS-R to confirm DoC diagnosis before enrollment. Existing CT or MRI-scans will be used to document structural lesions for neuronavigation-based targeting within 28 days before inclusion. Following screening phase, the legal surrogate of each eligible patient will be contacted for oral and written informed consent. After inclusion, every patient will first be enrolled in the crossover RCT protocol and will thus undergo four rTMS sessions. Based on the analysis of the patient’s best behavioral or electrophysiological response to either left DLPFC or left AG stimulation, the personalized protocol (4 weeks) will be started up to a week later.

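### In the 4-week trial the responder rule does not look back at the crossover CRS-R exams, so a sign already seen there can count as new

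*Protocol article*

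**What the plan says.** The Primary outcomes section of the protocol article defines clinical responders for a single crossover session and for the 4-week course in the same sentence, as "patients who will display new sign(s) of consciousness following treatment that was not present at baseline nor during the screening phase". The Study objectives and hypotheses section uses the same look-back: "any patient who displayed new sign(s) of consciousness following stimulation that was never displayed during the screening phase nor at baseline".

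The timing of the exams is fixed elsewhere in the article:

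- Screening & enrollment: patients are examined "at least twice within 10 days prior to inclusion", so screening ends before the crossover begins.
- Same section: "After inclusion, every patient will first be enrolled in the crossover RCT protocol and will thus undergo four rTMS sessions".
- Randomized crossover trial: "The CRS-R will be performed before and after each stimulation session".
- Personalized parallel trial: a one-week washout follows the crossover, and the CRS-R is then done at baseline and weekly for four weeks.
- Figure 3 legend: "Baseline (first day of stimulation, before the session) and post-treatment (last day of stimulation, after the session) assessments will include the CRS-R".

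**The concern.** The objectives section says that the sign must never have been displayed, so the intent is a sign that is new to the patient. In the crossover, screening and baseline come close to delivering that. In the 4-week trial they do not, because the crossover lies between the two points of the look-back and no section brings its exams in.

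Suppose a patient follows a command at a crossover exam, does not do so at the single day-1 exam, and does so again at the end of treatment. The rule labels this patient a responder to the 4-week course, on active or on sham, although the study's own records show the sign before the first of the 20 sessions.

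Three uses of the label are at stake:

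- the number of responders to the 4-week programme, which the Data analysis section plans to report;
- the responder phenotype, which is the third study aim;
- the machine-learning classifier of responder features, for which a separate publication is planned.

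The Discussion also hopes for more responders than in earlier RCTs. The sham arm does not correct that kind of external comparison.

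**Working it through.** The plan gives no figure for this point, so there is none to reproduce. The check has two parts.

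**1. Which exams are in the look-back.** Screening gives at least 2 exams and the day-1 baseline gives 1, so the stated look-back has at least 3. The crossover gives 4 sessions × 2 exams = 8, all after screening and before day 1. Of these, 4 precede a session, 2 follow a sham session and 2 follow an active session. Reading baseline as the crossover baseline would not help, because the post-session crossover exams would still be left out. The Figure 3 legend in any case fixes baseline at day 1 of the 4-week trial.

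**2. How much this could matter.** The documents give no rate for fluctuating signs, so the inputs are assumptions. A patient has a sign that is seen with constant probability q at each exam, exams are independent, and treatment has no effect. With L look-back exams and m later exams that can count:

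P(false new sign) = (1 − q)^L × [1 − (1 − q)^m]

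- L = 3: the stated rule at its minimum.
- L = 3 + 6 = 9: adding the pre-session and post-sham crossover exams.
- L = 3 + 8 = 11: adding all crossover exams.
- m = 1: only the last-day exam counts. m = 4: any weekly exam counts. The article does not settle which applies. The follow-up exams one and two weeks after treatment are left out here.

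Example for q = 0.2:

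- m = 1, L = 3: 0.8³ × 0.2 = 0.512 × 0.2 = 0.102
- m = 1, L = 9: 0.8⁹ × 0.2 = 0.134 × 0.2 = 0.027
- m = 4, L = 3: 0.512 × (1 − 0.8⁴) = 0.512 × 0.590 = 0.302
- m = 4, L = 9: 0.134 × 0.590 = 0.079

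| q | m | stated rule (L = 3) | six exams added (L = 9) | all eight added (L = 11) |
|---|---|---|---|---|
| 0.1 | 1 | 7.3% | 3.9% | 3.1% |
| 0.2 | 1 | 10.2% | 2.7% | 1.7% |
| 0.3 | 1 | 10.3% | 1.2% | 0.6% |
| 0.1 | 4 | 25.1% | 13.3% | 10.8% |
| 0.2 | 4 | 30.2% | 7.9% | 5.1% |
| 0.3 | 4 | 26.1% | 3.1% | 1.5% |

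Over a wider range, the stated rule gives 4.3% (m = 1) or 15.9% (m = 4) at q = 0.05, and 6.3% or 11.7% at q = 0.5.

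In this model, the share of false new signs that the six exams would have caught is 1 − (1 − q)⁶, which is 47%, 74% and 88% at q = 0.1, 0.2 and 0.3.

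**The case against.** The strongest objection is that a fresh baseline after a washout is a defensible choice for a separate parallel trial, and that crossover exams are not all evidence of spontaneous ability. Two of the eight follow active stimulation. A sign evoked by one active session, gone after the washout and back after 20 sessions at the same site may be a true response, and producing it is what the personalised trial is for. A rule that bars it would ask crossover responders for a further, different sign and would ask nothing extra of non-responders. This stands, and it is why the two post-active exams should not be in the main look-back. It does not excuse leaving out the other six.

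The reach is also limited. CRS-R total and index scores are the named primary outcome and do not use this rule. A sign still present on day 1 is already excluded, so only signs that lapsed are affected.

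A reader might draw stronger conclusions that the documents do not support:

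- *That the design selects such patients into the 4-week trial or into the active arm.* All patients go on and are randomised 2:1. Crossover response steers only the target site, and it may be an EEG response.
- *That the responder count is inflated by 25 to 30%.* Those figures apply to a patient who has a fluctuating sign, and only if any weekly exam counts. The share of such patients is unknown.
- *That the comparison with sham is biased towards active.* Both arms face the same rule. False labels may blur the comparison of responder proportions, but the documents give no basis for sizing this.

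**Conclusion.** The point holds in a limited form. If the plan is followed as written, a sign documented in the crossover can be counted as new in the 4-week trial, in either arm, provided it was absent at screening and on day 1. That follows from the text alone and needs no assumption.

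The size is illustrative. For a patient with a fluctuating sign and q between 0.1 and 0.3, the chance of a false new sign is about 7 to 10% with one counting exam and 25 to 30% with four. It rests on an assumed q, independent exams and only two screening exams; more screening exams would lower it. The effect on the trial's total responder count cannot be derived.

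The responder count, phenotype and classifier labels are affected; the score-based primary outcome is not. The change is worth making because the data that would prevent most of these labels are already collected.

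**What to change.** For the 4-week trial, count a sign as new only if it was absent at screening, at the day-1 baseline, and at every crossover exam done before a session or after a sham session. Report two further counts beside it: one under the current definition, and one under the strictest look-back with all eight crossover exams. The gap between the main and the strictest count shows how many responders depend on a sign already seen right after an active crossover session. Such signs may be true treatment responses.

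The cost is one sentence in the definition and two extra reported counts, with no new visits, exams or patients. Deriving the labels requires knowing which crossover sessions were sham, so this step should be done by whoever holds the sequence. The downside is somewhat fewer responders: a sign seen fleetingly at one of the six exams that later becomes stable would not count as new in the main analysis. It would still appear in the count under the current definition.
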